## LIST OF ABBREVIATIONS

|        |                                                    |
|--------|----------------------------------------------------|
| AE     | Adverse Event                                      |
| AGYW   | Adolescent Girls and Young Women                   |
| ART    | Antiretroviral therapy                             |
| CFR    | Code of Federal Regulations (USA)                  |
| CTC    | Care and Treatment Clinic                          |
| DSM    | Dar es Salaam Municipality                         |
| DSMB   | Data Safety and Monitoring Board                   |
| FDA    | Food and Drug Administration (USA)                 |
| GCLP   | Good Clinical Laboratory Practice                  |
| GCP    | Good Clinical Practice                             |
| HBsAg  | Hepatitis B surface Antigen                        |
| HIV    | Human Immunodeficiency Virus                       |
| HTC    | HIV Testing and Counselling                        |
| ICC    | Intraclass-Correlation Coefficient                 |
| ICH    | International Conference on Harmonisation          |
| IRB    | Institutional Review Board                         |
| ITT    | Intention To Treat                                 |
| LTFU   | Loss To Follow Up                                  |
| MDH    | Management and Development for Health              |
| MITT   | Modified Intention To Treat                        |
| MUHAS  | Muhimbili University of Health and Allied Sciences |
| MOP    | Manual of Procedures                               |
| NACP   | National AIDS Control Program                      |
| NIMR   | National Institute for Medical Research (Tanzania) |
| OHRP   | Office for Human Research Protection               |
| PEPFAR | President's Emergency Plan For AIDS Relief         |
| PI     | Principal Investigator                             |
| PHDP   | Positive Health Dignity Prevention                 |
| PrEP   | Pre-Exposure Prophylaxis                           |
| QC     | Quality Control                                    |
| SAE    | Serious Adverse Event                              |
| SAP    | Statistical Analysis Plan                          |
| SMS    | Short Message System                               |
| STI    | Sexually Transmitted Infections                    |
| TDF    | Tenofovir Disoproxil Fumarate                      |
| UP     | Unanticipated Problem                              |
| USAID  | United States Agency for International Development |
| WHO    | World Health Organization                          |

## 1. PROTOCOL ABSTRACT

|                      |                                                                                                                                                                                                                                                                                                                                                                                                                                                                                                                                                                                                                                                                                                                                                                                                                                                                                                                                                                                                                                                                                |
|----------------------|--------------------------------------------------------------------------------------------------------------------------------------------------------------------------------------------------------------------------------------------------------------------------------------------------------------------------------------------------------------------------------------------------------------------------------------------------------------------------------------------------------------------------------------------------------------------------------------------------------------------------------------------------------------------------------------------------------------------------------------------------------------------------------------------------------------------------------------------------------------------------------------------------------------------------------------------------------------------------------------------------------------------------------------------------------------------------------|
| Title:        | Demonstrating service delivery models for effective initiation and retention on PrEP among Barmaids in Dar es Salaam                                                                                                                                                                                                                                                                                                                                                                                                                                                                                                                                                                                                                                                                                                                                                                                                                                                                                                                                                           |
| Introduction: | 
In this double-randomized intervention study, participants will be provided with emtricitabine/tenofovir disoproxil as PrEP. Eligible participants will be randomized first to receive PrEP at their bar workplace or at a government clinic, and second to receive or not receive PrEP Champions intervention (physical and virtual support from an experienced PrEP user) to improve PrEP adherence.. We expect to screen 1204 barmaids in order to have at least 160 who are HIV negative and who agree to enroll in the study. After initial enrollment, follow-up visits will be scheduled every months. HIV testing will be performed at baseline, month 1, 4 and 6; TDF testing at months 2 and 6.
                                                                                                                                                                                                                                                                                                                                                               |
| Objectives:   | 
Primary objective 1: To assess whether workplace-based PrEP initiation for DSM barmaids at their bar of work increases the rate of PrEP initiation relative to initiation at healthcare facilities with the assistance of a peer navigator (standard of care).
 
Primary objective 2: To determine whether workplace-based initiation and provision of PrEP refills to barmaids in DSM at their bar of work increases PrEP retention and adherence relative to routine facility-based PrEP initiation and refilling at healthcare facilities.
 
Primary objective 3: To explore preferences for, willingness, and factors influencing uptake of Long-Acting injectable HIV PrEP among female barmaids in Ubungu Municipality.
 
Secondary objective 1: To assess whether receiving support by an omni-channel (physical and virtual) PrEP Champion, improves PrEP adherence relative to the national standard of care.
 
Secondary objective 2: To document the performance of a novel point of care urine assay as a measure of adherence to PrEP.
 |
| Endpoint:     | 
Primary endpoint 1: Proportion of those offered PrEP who are directly observed to initiate PrEP
 
Primary endpoint 2: Adherence to PrEP measured by drug level at 6 months post-enrollment
 
Primary endpoint 3: Thesis; Barmaids' preferences, willingness to use, factors influencing uptake of long-acting injectable HIV PrEP and feasibility of implementing injectable PrEP.
 
Secondary endpoint 1: Retention in PrEP care measured by refill rates at each study visit
 
Secondary endpoint 2: Performance of the urine assay for PrEP adherence will be documented qualitatively. Additionally, onsite test interpretation by health providers will be compared with the test's developers.
                                                                                                                                                                                                                                                                                                                                                |
| Population:   | 1204 women working in bars in Dar es Salaam, Tanzania aged over 15 years                                                                                                                                                                                                                                                                                                                                                                                                                                                                                                                                                                                                                                                                                                                                                                                                                                                                                                                                                                                                       |

|                                                |                                                                                                                                                                                                                                                                                                                                  |
|------------------------------------------------|----------------------------------------------------------------------------------------------------------------------------------------------------------------------------------------------------------------------------------------------------------------------------------------------------------------------------------|
| Phase:                                  | N/A                                                                                                                                                                                                                                                                                                                              |
| Number of Sites enrolling participants: | One                                                                                                                                                                                                                                                                                                                              |
| Description of Study Agent:             | The study will involve the provision of emtricitabine 200 mg and tenofovir disoproxil fumarate 300 mg, to be taken orally as a pill once per day for six months. This use is approved for use by the United States Food and Drug Administration (FDA) and recommended for use to prevent HIV infection by the WHO. |
| Study Duration:                         | Twelve months                                                                                                                                                                                                                                                                                                                    |
| Participant Duration:                   | Six months                                                                                                                                                                                                                                                                                                                       |

## 2. INTRODUCTION: BACKGROUND INFORMATION AND LITERATURE REVIEW

### 2.1 BACKGROUND INFORMATION

In Tanzania, there are 1.4 million people currently living with HIV, with a national prevalence of 4.7%. While the country has made considerable strides in addressing the epidemic since the first cases were reported in the 1980s, Adolescent Girls and Young Women (AGYW) continue to be disproportionately affected and vulnerable to HIV. In fact, HIV prevalence triples from 1.3% among adolescent girls aged 15-19, to 4.4% among young women aged 20-24 [1]. This age group bears the greatest HIV burden in the country. Despite being substantially more impacted by HIV, AGYW are often reluctant to seek sexual and reproductive health services due to past experiences of poor quality of care and stigma and discrimination from health care workers [2]. Therefore, more innovative, female-centered, and youth-friendly HIV prevention approaches are necessary.

In 1990, Stein [3] proposed user-dependent HIV prevention methods, specifically ones initiated and managed by women. Oral Pre-Exposure Prophylaxis (PrEP) – one such prevention method – involves the administration of a single antiretroviral (ARV) agent, or dual agents, to HIV-negative individuals prophylactically; to protect them from infection should they be exposed to an infective source. Following the first study of PrEP efficacy, among men who have sex with men (MSM) and transgendered women (TGW) reported in 2010, the concept of a daily pill (emtricitabine (FTC) and tenofovir (TDF), marketed as Truvada to prevent HIV infection has become increasingly accepted as a useful additional biomedical intervention offered to individuals in conjunction with regular testing, counseling, condoms and safe lubricants [4].

The WHO recommended the use of PrEP in 2015 as part of a comprehensive HIV prevention package – including HIV testing, voluntary medical male circumcision (VMMC), and harm reduction interventions for people who use injection drugs – for those at substantial risk for HIV acquisition. Results from trials have shown PrEP as highly efficacious, with a 92% protective effect when used as prescribed [5–9]. These same trials have also demonstrated adherence as key to efficacy, with more adherence to the pill conferring greater protection. Therefore adherence to daily oral PrEP is crucial, for the design and implementation of effective service delivery models for PrEP.

There are several ongoing and planned PrEP demonstration projects in Africa [10,11]. Of biomedical HIV prevention strategies that have been tested, daily oral PrEP has the greatest evidence for protection [12], although adherence was low in two placebo-controlled trials in young African women [13,14]. In Tanzania the use of PrEP was launched in 2018 as part of Tanzania's fourth Health Sector HIV and AIDS Strategic Plan (HSHSP IV 2017-2022), following suit of some other Sub-Saharan countries such as South Africa and Kenya. In the time following PrEP's introduction, the government has initiated demonstration studies to investigate the feasibility of implementing PrEP in the country. The National AIDS Control Program (NACP), through support from ICAP Columbia University USA, Jhpiego (implementing the *sauti* (voices) PrEP program), and HJF medical research international, has enrolled PrEP clients in 9 regions. The country intends to scale up PrEP availability to all 26 regions starting in April 2019, with focus on HIV key populations. Current estimates of PrEP users in Tanzania are between 7800-8300. Gilead's Truvada (TDF/FTC) has been registered and approved in Tanzania, while generic versions of TDF/FTC for prevention is under review (<https://www.prepwatch.org/country/tanzania/>).

PrEP requires a prescription, specialized counseling, regular HIV testing, and close clinical monitoring for side effects and seroconversion through frequent follow-up [15]. However, little evidence exists on the knowledge, attitudes, and perception of female barmaids toward PrEP in sub-Saharan Africa and nothing is known about barmaids' perceptions toward PrEP in Tanzania. Furthermore, because PrEP is still a relatively new biomedical intervention, it is necessary to understand the issues surrounding its implementation into health care systems and

people's perception to this implementation. Regular HIV testing at the time of PrEP initiation and then on an on-going basis, is required for the intervention.

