### **Randomization 1: PrEP delivery method**

We will randomly assign bars to one of two PrEP delivery groups: facility-based or workplace-based. All women enrolled onto PrEP from each bar will be assigned to their bars' study group, i.e. this is a cluster-randomized design. Bar-level clusters will be used to avoid study contamination and ensure smooth study operationalization.

**Group 1a. Facility-based PrEP delivery:** All HIV-negative participants in facility-based group bars will be offered the opportunity to initiate PrEP. If they agree to participate, they will be introduced to an assigned peer navigator. The peer navigator will arrange a time to escort the barmaid to their preferred health facility (from the list prepared by the study team) for PrEP services. At the facility, they will be started on emtricitabine/tenofovir disoproxil, with direct observation of the first dose. The study team will actively follow-up the clients to discontinue the participant from PrEP in case they show any signs of side effects. This practice of immediate initiation of treatment followed by discontinuation of treatment among participants with contraindications is comparable to Tanzanian's current guidelines for immediate initiation of ART in HIV-positive patients and PrEP implementation framework.

At the enrolment visit, participants will be scheduled for regular follow-up visits at the facility to monitor medication adherence and safety, once every 2 months, and to receive a PrEP prescription refill on monthly basis.. These visits will include HIV testing, creatinine levels, screening and treatment for STIs as required, and adherence counselling. All these services are standard of care for monitoring patients on treatment and fulfill monitoring requirements in national PrEP and HIV treatment guidelines [24].

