**Group 1b. Workplace-based PrEP delivery:** HIV-negative participants in workplace-based group bars will be offered the opportunity to initiate PrEP at the bar immediately. If they agree to participate, they will be started on emtricitabine/tenofovir disoproxil, with direct observation of the first dose. This initiation will be conducted by study healthcare staff who are allowed to prescribe ART as per Tanzania national policy. Again, should test results subsequently show that participants meet for side effects or other exclusion criteria, the study team will actively follow up to discontinue the participant from PrEP. All subsequent visits will be as in the facility-based group but carried out at the workplace with the assistance of the Community based HIV care providers. The Community based HIV care providers will provide refills; conduct monitoring,

and record inconveniences encountered – since this is an important part of the feasibility assessment for this mode of delivery.

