### **4.3.3 EXPLORATORY ENDPOINTS**

1. Level of HIV-related knowledge, including PrEP
2. Characteristics of those accepting and declining to initiate PrEP
3. Proportion of those initiating PrEP retained in care at each study visit
4. Proportion of those initiating PrEP reporting >85% adherence at each study visit
5. Proportion of those initiating PrEP reporting side-effects
6. Number of HIV seroconversions at each study visit
7. Change in number of sexual partners reported in past 30 days from initiation to each study visit
8. Proportion of women reporting consistent condom use at baseline and final visit
9. Proportion of those initiating PrEP with STI symptoms at each study visit
10. Proportion of those initiating PrEP receiving a routine follow-up.
11. Proportion of those initiating PrEP declining being part of the omni-channel PrEP Champions intervention at baseline and at each study visit.
12. Proportion of those initiating PrEP with Tenofovir urine levels compatible with weekly dosing, dosing in the past 2 to 3 days, and dosing within the past 24 hours.

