### 7.3. Study Schedule

#### 7.3.1 SCREENING

##### Recruitment and Screening visit

- Recruitment of barmaids for screening and PrEP intervention
- Obtain informed consent of potential participant verified by signature on screening informed consent form.
- Conduct screening questionnaire.
- Obtain demographic information and medical, medication, alcohol and tobacco use history.
- Review medical history to determine eligibility based on inclusion/exclusion criteria.
- Review medications history to determine eligibility based on inclusion/exclusion criteria.
- Perform medical examinations needed to determine eligibility based on inclusion/exclusion criteria. Specifically we will perform:
  - A point-of-care HIV test as part of standard HIV counselling and testing;
  - A point-of-care Hepatitis B surface antigen (HBsAg);and
  - Blood sample collection for a local, laboratory-based test of serum creatinine and syphilis.
- Schedule study visits for participants who are eligible and available for the duration of the study.

- The screening visit will require between 1.5 and 2 hours to complete

---

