### **7.3.2 ENROLLMENT/BASELINE**

#### **Baseline Visit (Visit 0, Month 0)**

- Obtain informed consent of potential participant verified by signature on study informed consent form.
- Verify inclusion/exclusion criteria.
- Division into the two study randomization groups 1 and 2
- Directly observe the first dose of emtricitabine/tenofovir disoproxil being taken and provide 28 (1 month) days of emtricitabine/tenofovir disoproxil.
- Counsel participant on adherence to emtricitabine/tenofovir disoproxil and need to contact the study if any changes in health arise.
- Conduct baseline questionnaire

---

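### Section 2.1 requires an HIV test when PrEP is started, but the only test scheduled before the first dose is at screening, with no stated maximum interval to Visit 0

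*Protocol*

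**What the plan says.** Section 2.1 of the protocol sets the requirement: "Regular HIV testing at the time of PrEP initiation and then on an on-going basis, is required for the intervention".

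The operational sections place the events as follows.

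- The screening visit (7.3.1) includes "A point-of-care HIV test as part of standard HIV counselling and testing".
- Visit 0 (7.3.2) instructs staff to "Directly observe the first dose of emtricitabine/tenofovir disoproxil being taken". Its list also has "Verify inclusion/exclusion criteria", but names no HIV test.
- The laboratory table (7.2) and the schedule of events (7.3.6) show HIV tests at screening and at months 1, 4 and 6. The schedule has a separate column for Baseline Visit 0, and its HIV-test cell is empty.

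Section 4.1 describes two routes to the first dose. For the facility arm: "The peer navigator will arrange a time to escort the barmaid to their preferred health facility". Women in workplace bars are "offered the opportunity to initiate PrEP at the bar immediately".

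Section 2.4.1 names drug resistance in a woman who is already HIV-positive as a risk of the drug, the first it lists, and relies on HIV testing to avoid it. For women with symptoms of possible acute infection, it delays the start by a month and calls for a second test. Section 5.2 also excludes women who report flu-like symptoms that could be acute HIV.

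**The concern.** Site staff will work from the visit lists and the schedule, not from the background section. If they follow those lists, a facility-arm woman is tested at her bar and takes her first tablet at a clinic on a later date, with no further test marked for that visit. The negative result that makes her eligible may by then be of any age that the protocol does not rule out. In the workplace arm, as section 4.1 describes it, test and offer of PrEP come together. The age of the last negative test at first dose can therefore differ by randomised arm.

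Two things are at stake. The first is the safeguard that section 2.4.1 relies on against resistance, which is weaker the older the test is at first dose. The second is interpretation. Exploratory endpoint 6 is the "Number of HIV seroconversions at each study visit". Unless the dates of the last negative test and of the first dose are known, a positive result at month 1 cannot be described as a possible infection before, rather than after, the start of PrEP.

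**Working it through.** The protocol gives no figure to reproduce on this point. The check is a comparison of passages, followed by a rough size.

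**1. Where the HIV test falls**

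| Protocol section | HIV test before or at first dose | HIV tests afterwards |
|---|---|---|
| 1 Abstract | baseline | months 1, 4, 6 |
| 2.1 | when PrEP is started | ongoing |
| 2.4.1 | baseline; second test only if symptoms suggest acute infection | months 2, 4 |
| 7.2 laboratory table | screening visit | months 1, 4, 6 |
| 7.3.1 to 7.3.4 visit lists | screening visit; none at Visit 0 | months 1, 4, 6 |
| 7.3.6 schedule | screening visit; Visit 0 cell empty | Visits 1, 4, 6 |

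The three operational sources agree with one another: the only scheduled test before dosing is at screening. They meet section 2.1 only if screening and first dose coincide. Section 4.1 makes that plausible in the workplace arm and not in the facility arm.

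The table also shows a second mismatch. Section 2.4.1 puts the follow-up tests at months 2 and 4, while the abstract, 7.2 and 7.3.6 put them at months 1, 4 and 6.

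**2. Length of the untested gap**

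Visits 1 to 6 each carry a window of 7 days either side (7.3.3, 7.3.4). No window links screening to Visit 0. Visit 1 is at day 30 ± 7, so the next test is at day 23 to 37 after the first dose. Hence:

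time between the last pre-dose test and the first on-drug test = (screening to Visit 0) + 23 to 37 days.

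By section 4.1 the first term is about 0 days in the workplace arm. In the facility arm it has no stated maximum.

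**3. Rough size**

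- Facility initiators: 40 + 40 = 80 (table in section 9.4.1).
- Incidence: 2 to 5 per 100 woman-years. This is an assumption; the protocol gives none.
- Interval from bar test to first dose: 1 to 8 weeks for every facility initiator. This is also an assumption.

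Expected infections in the interval = 80 × incidence × weeks / 52.

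| Interval | Incidence 0.02 | Incidence 0.05 |
|---|---|---|
| 1 week | 80 × 0.02 × 1/52 = 0.03 | 80 × 0.05 × 1/52 = 0.08 |
| 4 weeks | 80 × 0.02 × 4/52 = 0.12 | 80 × 0.05 × 4/52 = 0.31 |
| 8 weeks | 80 × 0.02 × 8/52 = 0.25 | 80 × 0.05 × 8/52 = 0.62 |

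These figures count only infections acquired between test and dose. They do not include infections already present but missed by the screening test, which can occur in either arm.

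**The case against.** The strongest reply is that section 2.1 is background. It says what PrEP in general requires and assigns no test to Visit 0. A negative test before the first dose, then repeat tests, could be read as satisfying it. That reading works where screening and start fall on the same day. It does not work for a clinic start arranged for later with no stated limit, so the objection narrows the point to the facility arm without removing it.

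The protocol also has other safeguards. Eligibility is verified again at Visit 0, symptoms of possible acute infection exclude a woman or trigger a delay and a second test, month 1 brings another test, and section 5.4.1 lists a positive test as a ground for ending participation. These count. But the symptom checks do not reach an infection without symptoms, the Visit 0 check names no test, and the month-1 test comes after about a month on drug.

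The contrast between arms rests on section 4.1 alone. Section 7.3 lists screening and Visit 0 as separate visits for both arms, so immediate workplace dosing is described but not scheduled. Immediate against linked initiation is also the comparison under study. The difference in timing is therefore not itself a defect; the unstated place of the HIV test within it is.

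Three stronger readings are tempting and should not be drawn.

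- A reader might infer that an unlimited interval is allowed. The protocol is silent; it states no maximum, and the facility arm uses active, escorted linkage.
- A reader might infer that the abstract and section 2.4.1, which place a test at *baseline*, contradict the schedule. The protocol also uses that word for hepatitis B and creatinine tests that it schedules at screening (2.4.1, 7.2), so it can mean screening here too.
- A reader might infer that exploratory endpoint 6 is biased in favour of workplace delivery. The protocol states no comparison between arms for that endpoint, and a recent infection missed at screening could surface at month 1 in either arm.

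**Conclusion.** The point holds as an inconsistency in the protocol that should be corrected. Section 2.1 calls for an HIV test when PrEP is started. The laboratory table, the Visit 0 list and the schedule place the only pre-dose test at screening, with no stated maximum interval to the first dose. The consequence falls mainly on the facility arm. The follow-up test months in section 2.4.1 also disagree with the rest of the protocol.

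Its size is modest. About 0.03 to 0.6 infections would be expected between test and first dose among 80 facility initiators. That range rests on assumed incidence and intervals, and on the initiation numbers in section 9.4.1 being reached. No primary or secondary endpoint is affected. The case for correction is that the safeguard concerned is the one section 2.4.1 relies on for the first risk it names, and that the correction is cheap.

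**What to change.** - Reconcile sections 2.1, 2.4.1 and 4.1 with 7.2, 7.3.1, 7.3.2 and 7.3.6, so that the schedule shows for each arm when the required HIV test takes place relative to the first dose. Which clinical rule applies is for the clinical team.
- In the same edit, align the follow-up test months in section 2.4.1 with those in the abstract, 7.2 and 7.3.6, whichever set is intended.
- Record the date of the last negative HIV test and the date of the first dose for every woman who starts PrEP. Endpoint 6 already counts seroconversions by visit, so no new endpoint is needed. The dates let a positive at month 1 be described as a possible infection before the first dose.

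The cost is one protocol correction and two dates on the case report form. Neither the sample size nor the primary analyses change. The one consequence for reporting is that some month-1 positives may no longer be presented simply as seroconversions on PrEP.
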